## Abstract

**Background:**

Epidermal growth factor receptor tyrosine kinase inhibitors (EGFR-TKIs), such as gefitinib, have achieved good efficacy in EGFR mutation-positive non-small-cell lung cancer (NSCLC) patients, but eventual drug resistance is inevitable. Thus, new TKI-based combination therapies should be urgently explored to extend the overall survival time of these patients. CD8 + CD56+ natural killer T (NKT) cells are a natural and unique subset of lymphocytes in humans that present characteristics of T and NK cells and exert cytotoxicity on tumour cells in a granzyme B-dependent manner. The aim of this trial was to explore the efficacy and safety of CD8 + CD56+ NKT cell immunotherapy combined with gefitinib in patients with advanced EGFR-mutated NSCLC.

**Methods:**

The study was designed as a prospective, randomized, controlled, open-label, phase I/II trial that includes 30 patients with EGFR mutation-positive stage III/IV NSCLC. All patients will be randomized in blocks at a 1:1 ratio and treated with gefitinib 250 mg/day monotherapy or combination therapy with allogeneic CD8 + CD56+ NKT cell infusions twice per month for 12 cycles or until disease progression occurs. The effectiveness of this treatment will be evaluated based on by progression-free survival (PFS), the time to progression (TTP), overall response rate (ORR), disease control rate (DCR) and overall survival (OS). The safety of the trail is being assessed based on adverse events (AEs). Recruitment and data collection, which started in December 2017, are ongoing.

**Discussion:**

Although immunotherapy, including programmed death-1/programmed death-1 ligand (PD-1/PD-L1) immunotherapy, has been used for NSCLC treatment with or without EGFR-TKIs, its clear efficacy still has not been shown. Assessing the safety and therapeutic potential of allogeneic CD8 + CD56+ NKT killer cells in combination with EGFR-TKIs in NSCLC will be of great interest.

**Trial registration:**

This trial (Phase I/II Trails of NKT Cell in Combination With Gefitinib For Non Small Cell Lung Cancer) was registered on 21 November 2017 with www.chictr.org.cn, ChiCTR-IIR-17013471.

**Supplementary Information:**

The online version contains supplementary material available at 10.1186/s12885-021-08590-1.

## Background

### EGFR-TKI and NSCLC

According to a status report on the worldwide cancer burden in 2018, lung cancer remains the leading cause of cancer incidence and mortality [1]. Among the approximately 2 million new cases each year, 80–85% of new cases are non-small-cell lung cancer (NSCLC), such as adenocarcinoma, squamous cell carcinoma, and large cell carcinoma, and 15–20% are small-cell lung cancer. Platinum chemotherapy has been the main systemic therapy for patients with advanced NSCLC over the past few decades [2]. In 2004, published data showed that somatic mutations in the epidermal growth factor receptor (EGFR) gene are detected in 30–40% of NSCLCs in Asian patients, and deletions in exon 19 and L858R in exon 21 account for 90% of these activating EGFR mutations [3]. Several epidermal growth factor receptor tyrosine kinase inhibitors (EGFR-TKIs), such as gefitinib, have shown a higher response rate and longer progression-free survival (PFS) than platinum chemotherapy in patients with EGFR mutations and have become a first-line treatment for advanced NSCLC [4, 5]. Thus, these key studies clarified the relationship between EGFR mutations and the efficacy of EGFR-TKI treatment, providing opportunities for the personalised treatment of advanced NSCLC. Though the majority of patients with mutation-positive NSCLC respond to treatment with EGFR-TKIs, the long-term use of EGFR-TKIs for approximately 9–12 months eventually leads to drug resistance, which limits their clinical benefits [6–8]. In addition, co-mutation is common in NSCLC patients with EGFR mutations, and the efficacy of first-line TKI monotherapy in NSCLC patients with EGFR co-mutations is significantly worse than that in patients without co-mutations [9]. Therefore, for EGFR mutation-positive patients, TKI-based combination therapy, especially with immunotherapy, needs to be further explored [10].

### Immunotherapy and NSCLC

Immunotherapy is a novel, promising treatment for cancers that uses different effective elements of the immune system, such as cytokines, antibodies and effector immune cells. Currently, immune checkpoint inhibitors, anti-programmed death-1 (anti-PD-1) and anti-programmed death-1 ligand (anti-PD-L1), have shown promising effects for treating tumours [11]. Several combination trials of EGFR-TKIs and immune checkpoint inhibitors in NSCLC are also recruiting participants. Nevertheless, some evidence has shown that anti-PD-1 therapy has no additional effects with EGFR-TKI treatment because of the lower expression levels of PD-1 among EGFR-mutant NSCLC patients [12, 13]. Therefore, more evidence is needed on the actual synergistic effects of anti-PD-1 and anti-PD-L1 with EGFR-TKIs [14, 15].

## Rationale

In the immune system, there are different types of killer cells that play roles in immune surveillance. Therefore, methods to isolate these cells from the blood, culture and expand them with or without gene editing in the laboratory, and finally infuse these killer cells into the body of patients to exert anti-tumour effects have also been designed for cancer immunotherapy. Currently, the types of killer cells used in cellular immunotherapy are CD8+ T cells including tumour-infiltrating lymphocytes (TILs) and chimeric antigen receptor T (CAR-T) cells, NK cells, and natural killer T (NKT) cells. NKT cells are a subset of CD1d-restricted T cells at the interface between the innate and adaptive immune systems and have characteristics of both conventional T cells and NK cells [16]. Classical NKT cells with invariant TCR α chains were first identified in mice in 1990 and subdivided into different subsets that have a variety of roles in cancer and other diseases [17, 18]. Nevertheless, in some studies, NKT cells have also been identified with flow cytometry analysis with the cell phenotype of CD3 + CD56+ or CD8 + CD56+ in humans and CD3 + NK1.1+ or CD8 + NK1.1+ in mice. Though the definition of these CD3+ subpopulations as NKT cells is still debatable, and they are even referred to as “NKT-like” cells, these cells show activity in innate immunity [19–23]. The work from Sergey S. Seregin showed that CD8 + NK1.1+ cells, not CD8 + NK1.1- cells, have the ability to provide a rapid innate immune response through Ag-independent IFN-γ production and granzyme B degranulation in pathogen infection [22, 23]. Our previous data also demonstrated that CD8 + NK1.1+ cells exerted NK- and CTL-like antitumour effects through the elimination of both tumour cells and myeloid-derived suppressor cells (MDSCs) in a granzyme B-dependent manner [24]. Moreover, we further proved that CD8 + CD56+ cells in humans have similar cytotoxicity to CD8 + NK1.1+ cells in mice and can be effectively expanded in vitro for tumour immunotherapy. However, it is unclear whether these CD8 + CD56+ NKT cells have synergistic effects with EGFR-TKIs, extend PFS and delay resistance to EGFR-TKIs in NSCLCs. Thus, a trial assessing the efficacy of CD8 + CD56+ NKT cells with gefitinib for patients with EGFR mutations is needed.

## Methods

### Objectives

The aim of this trial is to assess whether the proposed allogeneic NKT cell adoptive transfer, when given in combination with gefitinib, warrants further consideration based on its safety and efficacy for the treatment of advanced EGFR-mutant NSCLCs. Effectiveness is being evaluated by PFS, the time to progression (TTP), overall response rate(ORR), disease control rate (DCR) and overall survival (OS). Safety assessment is based on adverse events (AEs), vital signs, clinical laboratory tests, such as haematologic, blood biochemical and urine analysis, and electrocardiograms.

### Trail design

The study protocol (Issue date: 9 September 2017, protocol amendment number: v1.2) was written in accordance with the Standard Protocol Items: Recommendations for Interventional Trials (SPIRIT) 2013 Statement [25]. A SPIRIT checklist is provided in the supplementary material (Additional file 1: Table S1). This early exploratory phase I/II clinical trial was initiated by the investigators and supported by the key research and development special funding of the Jiangsu Science and Technology Bureau for social development. The affiliated Hospital of Jiangsu University is responsible for clinical research.

The study was designed as a prospective, randomized, open-label, controlled phase I/II parallel-group trial to explore the efficacy and safety of NKT cell infusion immunotherapy combined with gefitinib versus gefitinib monotherapy in patients with advanced EGFR-mutated NSCLC (Fig. 1). This study will recruit 30 participants with advanced NSCLC who meet the inclusion/exclusion criteria and individually randomize them at a 1:1 ratio based on the trial schedule (Fig. 1). The two arms of the trial are as follows (Table 1):
Experimental group (Arm A): 250 mg gefitinib orally once daily. After being effectively treated with gefitinib for 8 weeks, allogeneic NKT cell transfer treatment will be added every 4 weeks, with a total cell number of 1 × 10^10^ ± 15% divided into two infusions with an interval of 3 days. This process will be repeated for a total of 16 weeks, which is defined as one-cell therapy cycle, and then NKT cell infusion treatment will be suspended for 4 weeks. After that, this cycle will be continually repeated three times (total of 60 weeks) or stopped when disease progression/unacceptable toxicity/participant choice occurs (Table 1).Control group (Arm B): 250 mg gefitinib orally once daily until disease progression/unacceptable toxicity/participant choice occurs.

**Fig. 1 Fig1:**
[figure not shown]
Flow diagram of this parallel randomised trial. EGFR: epidermal growth factor receptor; PFS: progression-free survival; TTP: time to progression; ORR: overall response rate; DCR: disease control rate; OS: overall survival

**Table 1 Tab1:** Treatment schedule for the frequency of gefitinib and NKT cell in both arms of the trail

Week-4-0	Week 0–8			One cell therapy cycle				
				Week 9–12	Week 13–16	Week 17–20	Week 21–24	Week 25–28
Screening	Randomization	Experimental group (Arm A)	Donor selection, PBMCs^a^ acquisition and NKT cell preparation	NKT infusion	NKT infusion	NKT infusion	NKT infusion	Suspend
			Gefitinib orally once daily					
		Control group (Arm B)	Gefitinib orally once daily					

This schedule use one cell therapy cycle as an example, and the follow-up treatment is carried out according to the same cell therapy cycle until the trial is terminated after the disease has progressed or complete three cell therapy cycles (total 60 weeks). ^a^*PBMCs* peripheral blood mononuclear cells

### Study population

The main participant inclusion and exclusion criteria are shown in Table 2. This trial aims to include only patients with advanced NSCLC (III/IV) harbouring mutated EGFR (exon 19 deletion or exon 21 Leu858 Arg point mutation) who can be effectively treated with gefitinib.

**Table 2 Tab2:** Eligibility criteria

Key inclusion criteria	Key exclusion criteria
• Histological diagnosis of advanced non-small cell lung cancer (III/IV) with measurable lesions; • No other chemotherapy and radiation therapy to be planned recently. I • Aged 18 to 75 years, male or female; • Evidence of activating mutations of EGFR(exon 19 deletion or exon 21 Leu858Arg point mutation)and can be treated with gefitinib; • Patients must have a Karnofsky performance status greater than or equal to 80%; • There is no disease progression after being treated with gefitinib for 8 weeks; • Adequate bone marrow reserve and adequate live and renal functions: hemoglobin ≥9 g/dL, absolute neutrophil (segmented and bands) count (ANC) ≥ 1.5 × 10^9^/L, lymphocytes count ≥ lower limit of normal reference value, platelet count ≥8 × l0^10^/L, serum creatinine ≤1.5 × high limit of normal reference value, Serum bilirubin ≤2 × upper limit of normal reference value, both of AST/ALT ≤2 × upper limit of normal reference value; • Women of childbearing potential must have a negative pregnancy test (within 7 days) prior to receiving treatment of study agent; • Life expectancy greater than 12 months; • Patients have ability to understand and subscribe of informed consent.	• Organ dysfunction defined as follows: significant cardiovascular disease (i.e. New York Heart Association [NYHA] class 3 congestive heart failure, myocardial infarction within the past 6 months, unstable angina, coronary angioplasty within the past 6 months, uncontrolled atrial or ventricular cardiac arrhythmias); Liver function grading Child-Pugh C; renal function failure or uremia; respiratory failure; disturbance of consciousness; • Patients with genetic diseases; • Known central nervous system tumors including metastatic brain disease, unless treated and stable; • Suffering from lymphoma, leukemia and myelodysplastic syndrome (MDS); • Serious infections requiring antibiotics treatment, bleeding disorders; • History of bone marrow or stem cell transplantation, or allograft transplantation; • Patients with immunodeficiency disease or autoimmune disease, except vitiligo; • Patients with allergy history, especially allergy to heterologous proteins; • Uncontrolled infectious diseases and other serious diseases, such as patients with HIV positive, active HBV and HCV hepatitis; • Patients with chronic disease which is undergoing immune reagents or hormone therapy (Topical or inhalational corticosteroids are permitted); • Patients with concurrent chemotherapy or in five half-life periods of the used chemotherapy drugs; • Pregnant or breast-feeding women; • Mental impairment or addictive disorders that may interfere the ability to sign informed consent; • Lack of availability for immunological and clinical follow-up assessment.

This is also an exploratory study to test the safety and efficacy of the intravenous infusion of CD8 + CD56+ NKT cells, which replicates a planned larger study in at a smaller scale. Some authors have put forward suggestions on the sample size of pilot trials, specifically, 10 [26], 12 [27], or 15 [28] per group and a total of at least 20 participants [29]. According to a sample size “rule of thumb” of 30, the number of patients was designated as 15 patients in the experimental group and 15 patients in the control group, with a total sample size of 30 patients in this study. Although the power of this study is inadequate for evaluating clinical efficacy, the estimation of the efficacy of NKT cell immunotherapy combined with gefitinib and gefitinib alone will enable follow-up studies to calculate the efficacy more accurately.

### Randomization

After the subjects are registered (and before any trial treatment), the subjects will be randomly assigned to the experimental group (Arm A) or the control group (Arm B) at a proportion of 1:1. The method of block randomization will be used to randomize the subjects into the groups. The random number table will be generated by statistics experts.

### Preparation and administration of NKT cells

In this study, healthy immediate family members of the patient will be selected as donors for peripheral blood of nuclear cell (PBMC) collection and NKT cell preparation. PBMCs of the donor will be collected by an automatic blood cell separator and then frozen in liquid nitrogen. In the treatment phase of the study, PBMCs will be thawed, cultured and expanded with NKT complete medium with a protocol specially developed by the Institute of Cell Therapy, Tsinghua University, China. Prior to cell infusion, the quality of expanded NKT cells will be tested based on the cell number, purity, viability and sterility. The criteria of the tested cells included viability ≥90%, CD8+ ≥60%, and a minimum of 20% CD8 + CD56+ NKT cells. Along with gefitinib treatment in both Arms A and B, all patients in Arm A will intravenously receive 1 × 10^10^ expanded cells over 1 month with an interval of 3 days according to the schedule in Table 1. At the end of the cell transfusion, the subject will lie still and will be observed for 1 h, and their normal activities can be resumed if there is no discomfort or other adverse reactions.

## Assessments

A schedule of procedures and assessments is shown in Additional file 2: Table S2.

Several assessments will be used for the evaluation of therapeutic effects, including tumour lesion measurements, patient quality of life scores, and the detection of serum tumour markers, such as CEA. For tumour lesion detection, according to the Response Evaluation Criteria in Solid Tumors version 1.1 (RECIST Version 1.1), computed tomography (CT) will be used to measure the size of solid tumours during screening, treatment and follow-up in the study. All baseline assessments of the tumour focus size should be completed as close to the start of treatment as possible. Additionally, the KPS score and EORTC QLQ-C30-LC13 score will be evaluated to assess the quality of life of patients with lung cancer in all stages.

AEs, vital signs and safety laboratory examinations will be used for safety evaluation. The severity of AEs will be graded using a modified version of The Common Terminology Criteria for AEs (CTCAE v5.0), reported and addressed at any time during the course of the study. Nevertheless, vital signs, including blood pressure, body temperature, respiration and heart rate, will be monitored during all visits, and routine safety laboratory examinations are detailed in Table S2.

## Outcomes

### Primary effectiveness endpoint

The efficacy will be evaluated based on PFS, which is defined as the time from randomization to the first recording of disease progression (as defined by RECIST v1.1) or the death of the patient. Patients who are still alive and have no progression as of the date of analysis will be recorded as the date of their last imaging evaluation.

### Secondary effectiveness endpoints

TPP: the length of time from the date of randomization to tumour progression based on RECIST v1.1 criteria.

ORR: the proportion of participants with complete remission and partial remission, as judged by RECIST v1.1.

DCR: the proportion of participants with an objective response and stable disease, as defined by RECIST v1.1.

OS: defined as the time from the beginning of randomization to death from any cause. For patients who are still alive on the date of analysis, the date of their last contact will be recorded as the endpoint.

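### Read as best response from the pre-gefitinib baseline, DCR is settled at week 8, before any NKT cells are given; ORR is diluted equally in both arms

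*Protocol article*

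**What the plan says.** All places are in the protocol article.

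- **Endpoints (Secondary effectiveness endpoints).** DCR is "the proportion of participants with an objective response and stable disease, as defined by RECIST v1.1". ORR is "the proportion of participants with complete remission and partial remission, as judged by RECIST v1.1". Neither has a visit or a best-response rule.
- **Eligibility (Study population, Table 2).** One inclusion criterion reads "There is no disease progression after being treated with gefitinib for 8 weeks".
- **Start of cells (Trail design).** For Arm A: "After being effectively treated with gefitinib for 8 weeks, allogeneic NKT cell transfer treatment will be added every 4 weeks". Table 1 places the first infusions in weeks 9–12.
- **Tumour baseline (Assessments).** "All baseline assessments of the tumour focus size should be completed as close to the start of treatment as possible". No new baseline at week 8 is described.
- **Randomisation (Randomization).** Allocation is placed early: "After the subjects are registered (and before any trial treatment". Table 1 agrees, since its week 0–8 block already shows an Arm A activity, "Donor selection, PBMCs^a^ acquisition and NKT cell preparation".
- **Analysis (Statistical analysis).** ORR and DCR are compared between arms by Fisher's exact test, with one-sided tests at 0.05. The full analysis set is to stay close to intention to treat. Missing values of the main variables are filled by LOCF.

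**The concern.** The trial asks what the cells add to gefitinib. A between-arm endpoint can answer that only if its value can still change once cells start. Disease control is both an entry condition at week 8 and, through DCR, an efficacy outcome counted from before gefitinib. A patient who had stable disease at week 8 and progressed at week 12 would still have a best response of stable disease and would count as a DCR success, in either arm. The comparison would then describe the gefitinib-only period.

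The Study population section says the estimates from this trial are meant to inform follow-up studies. A DCR already determined at week 8 would be a poor input for that purpose at any sample size.

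ORR shares the feature in a weaker form. Responses reached on gefitinib alone count in both arms, so fewer patients can still show a difference.

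**Working it through.** **Inputs from the document.** 15 + 15 = 30 patients, which agrees with "with a total sample size of 30 patients in this study"; allocation 1:1; Fisher's exact test; one-sided; alpha 0.05; cells from week 9. The total comes from a rule of thumb. No response rate, DCR or power is stated, so there is no planned figure to reproduce. Every rate below is an assumption. Power is exact, summed over two binomials with n = 15 each.

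**1. DCR as best response, eligible patients only.** An evaluable patient with no progression at week 8 has CR, PR or SD. Best response can therefore not be progression, whatever happens later. The result is 15/15 v 15/15, Fisher p = 1.0, and power is 0 for any effect of the cells.

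**2. DCR as best response, all patients randomised at week 0.** Let a share e progress by week 8 in each arm. DCR is then 1 − e in both arms, and cells given later cannot alter it. The probability of p < 0.05 favouring Arm A is:

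| e (assumed) | expected early progressors per arm, 15e | probability of p < 0.05 |
|---|---|---|
| 5% | 0.75 | 0.003 |
| 10% | 1.5 | 0.012 |
| 15% | 2.25 | 0.020 |
| 20% | 3 | 0.022 |

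All of this is false positive. For scale, if Arm A had 15/15, Arm B would need 11/15 or fewer for significance (p = 0.0498; 12/15 gives 0.112).

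**3. DCR as status at a fixed time after cells start.** The arms can now differ.

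| Arm B v Arm A (assumed) | power |
|---|---|
| 50% v 70% | 0.18 |
| 40% v 70% | 0.36 |
| 50% v 80% | 0.37 |
| 30% v 70% | 0.59 |
| 50% v 90% | 0.67 |

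The endpoint is weakly powered but informative.

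**4. ORR from the pre-gefitinib baseline.** Let r be the response rate at week 8, and let l and c be the later conversion rates of non-responders in Arms B and A.

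ORR(B) = r + (1 − r)l; ORR(A) = r + (1 − r)c; difference = (1 − r)(c − l).

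With l = 10% and c = 50%, a 40-point effect on conversion:

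| r (assumed) | ORR, B v A | difference (points) | power |
|---|---|---|---|
| 0% | 10% v 50% | 40 | 0.67 |
| 40% | 46% v 70% | 24 | 0.24 |
| 50% | 55% v 75% | 20 | 0.18 |
| 60% | 64% v 80% | 16 | 0.14 |
| 70% | 73% v 85% | 12 | 0.11 |
| 80% | 82% v 90% | 8 | 0.07 |

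The difference keeps its sign and is zero when c = l. This is dilution without bias.

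**The case against.** A reader might infer that DCR cannot show an effect of the cells at all, that it is 100% in both arms by construction, and that ORR fails with it. The documents do not support that, for these reasons.

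- **No best-response rule is stated.** The Statistical analysis section speaks of efficacy being evaluated at the endpoint, which leaves an end-of-study reading open. Step 3 shows that DCR can then differ. This stands and limits the point to one reading. However, the phrase sits in a sentence on missing data, gives no date and does not define DCR.
- **15/15 v 15/15 is not guaranteed.** With randomisation before treatment and a full analysis set close to intention to treat, week-8 progressors may be counted. This stands, but on the best-response reading it does not make DCR informative (step 2).
- **Enrolment and baseline might both follow the 8 weeks of gefitinib.** The problem would then largely disappear for both endpoints. The eligibility criterion points that way; the Randomization section and Table 1 point the other way. The contradiction is real and has to be resolved.
- **ORR is protected by the concurrent gefitinib control.** This stands: the loss is equal in both arms.
- **A high DCR in Arm A might be taken for success.** The planned comparison would show a similarly high figure in Arm B, so this risk is modest.
- **Details may be elsewhere.** The assessment schedule (Table S2) and the full protocol are not shown and may fix the visits. For that reason the point rests on how the stated definition, entry criterion and treatment schedule combine, and not on a missing detail. Confidence is medium.

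**Conclusion.** The point holds in a conditional form. If DCR is best response from the pre-gefitinib baseline, the week-8 entry criterion settles it before the first infusion, and the Fisher comparison carries no information on the cells, whether or not early progressors are kept. If DCR is read as status at a later time, the problem does not arise, but the published text does not commit to that reading.

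ORR is neither biased nor uninformative. It is diluted by (1 − r): for an assumed 40-point effect on later conversion, the visible difference is 20 points at r = 50% and 12 points at r = 70%.

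Severity is minor to moderate. Only secondary endpoints are affected, in an exploratory 30-patient trial that itself calls its power inadequate for clinical efficacy. The DCR conclusion on the best-response reading needs no assumed rate beyond evaluable scans at week 8. The power and dilution figures rest wholly on assumed rates.

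**What to change.** 1. For the between-arm comparison, define DCR as the proportion of all randomised patients alive and progression-free at one fixed visit after cells start. Week 28 is one example, the end of the first cell therapy cycle as drawn in Table 1.
2. State that a week-8 status is not carried forward as disease control. Otherwise LOCF, if applied to DCR, would count a patient with no later scan as a success on the strength of gefitinib alone.
3. Keep ORR from the pre-gefitinib baseline in all randomised patients. Add, as supportive description by arm, the responses first reached after week 8. Making ORR from a week-8 baseline the main comparison is debatable: it conditions on status after randomisation, and a complete responder at week 8 has no new response to gain.
4. Reconcile the Table 2 criterion with the Randomization section on whether allocation precedes the 8 weeks of gefitinib, so that the denominator is clear.

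**Cost.** This is a change of wording and needs no more patients. Whether a scan already falls at the chosen visit has to be checked against Table S2. The DCR figure will look less favourable, and it will overlap with the Kaplan-Meier PFS estimate at the same time point.
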